### Sample size

Based on preliminary studies, we can expect a mean standardized difference between those in the physical activity intervention group and those allocated to a control group (usual care) of 1.8 in the PPT. A more conservative effect size has been used in sample size calculations for this study to accommodate for: a) the inclusion of a social comparator arm in this study rather than no intervention (usual care) and b) the potential of a clustering effect in the single site pilot study. A total of 46 HD patients (23 per group) are sufficient to detect a more conservative standardized difference of 1.0 at the final measurement point, with a power of 90% and α of 0.05. We aim to recruit 62 subjects in total to allow for 25% loss to follow-up, based on retention rates from our previous studies. This will allow us to estimate any proportion to within 14.4 percentage points either side, using a 95% confidence interval.

### Fidelity

Intervention fidelity will be assessed in the following ways. On completion of each session, the coach will complete an intervention implementation checklist, reporting on the component activities of the intervention. At least one of the physical coaching sessions per participant will be audio or video recorded. The transcripts of these recordings will be used to analyze the quality of the intervention delivery. Fidelity of the coach interpersonal interactions will be measured by assessing the extent to which the coach’s interactions with the participant adhered to three elements of SDT, namely autonomy, competence and relatedness. Data from the PAS Healthcare Climate Questionnaire
[34] completed by participants at assessment two will provide a measure of the individual coach’s perceived interaction style. Coach records and diaries will provide an assessment of use of the exercise DVD and the purpose-developed physical activity workbook.

### Data management

All assessment and intervention data will be entered by site staff to a study-specific online database, accessed via password-protected iPads (Apple Distribution International, [name]) provided to each site. Sites will be provided with paper versions of the assessment and intervention forms to be used as a backup, but it is anticipated that most sites will enter data directly into the database.

Using the online database for data entry will reduce burden on site staff, and allows for immediate validation checks upon data entry, which will prompt staff to address any questions which have been missed or values which appear to be outside of an anticipated range. Site staff will have their own individual login details, which will ensure that they are only able to access forms and database functions which are appropriate for their staff role. Data monitoring will take place on 100% of completed forms shortly after submission, allowing for timely query generation and resolution and the minimization of missing forms or data.

In addition to being used for data entry, study iPads offer a number of benefits related to training, support and data monitoring. Following site initiation visits, site staff will be able to use the iPad to record videos of practice assessments, for instance, and send these to study members for feedback. The iPad can also be used by site staff to communicate with study members via Skype, allowing for ongoing support in delivering the intervention. Finally, the iPad can be used to audio record selected intervention sessions, which will be used for the aforementioned assessment of intervention fidelity.

### Safety monitoring

An adverse event (AE) is defined as any untoward medical occurrence in a trial participant. A serious adverse event (SAE) is any untoward and unexpected medical occurrence or effect that results in death; is life-threatening (refers to an event during which the participant was at risk of death at the time of the event); requires hospitalization, or prolongation of existing hospitalization; results in persistent or significant disability or incapacity, or is a congenital abnormality or birth defect. We do not anticipate any SAEs in this trial cohort, although there is a chance that some individuals with HD may require hospitalization in relation to the course of their disease. The most likely reasons for unrelated hospitalization in any person with HD would be due to respiratory problems and fractures due to falls. Falls are an expected AE as part of the clinical condition at this stage of the disease. Related SAEs or AEs are defined as any event that results from administration of any of the research procedures that are considered causal to the research process or intervention. While falls can occur in people with Huntington’s disease, we do not anticipate any increase in fall risk from the ENGAGE-HD physical activity intervention. Any falls will be recorded routinely by the research team and submitted for assessment of relatedness as part of the study protocol. The proposed activity intervention is low-to-moderate intensity and does not involve any heavy load-bearing exercise, heavy eccentric muscle activity or high intensity activities. However, some minor muscle soreness or musculoskeletal strain may occur in the few days following the initiation of physical activity. This would normally resolve spontaneously and would not require any specific interventions or additional medical care, but will be noted as a potential expected related AE if reported. All AEs, related adverse events (RAEs) and SAEs will be recorded using a standard template and reported in line with standard operating procedures.

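### The SAE definition makes seriousness depend on the event being unexpected, so a fall with fracture and admission can be left out of the SAE count

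*Protocol article*

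**What the plan says.** All of the relevant wording is in Safety monitoring.

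- Adverse event: "An adverse event (AE) is defined as any untoward medical occurrence in a trial participant". Expectedness plays no part.
- Serious adverse event: "A serious adverse event (SAE) is any untoward and unexpected medical occurrence or effect that results in death". The sentence continues through the remaining criteria, including "requires hospitalization, or prolongation of existing hospitalization", and the word *unexpected* governs all of them.
- Anticipated SAEs, in the very next sentence: "We do not anticipate any SAEs in this trial cohort, although there is a chance that some individuals with HD may require hospitalization" because of the course of their disease.
- Likely admissions: "The most likely reasons for unrelated hospitalization in any person with HD would be due to respiratory problems and fractures due to falls".
- Expectedness of falls: "Falls are an expected AE as part of the clinical condition at this stage of the disease".
- Handling of falls: "Any falls will be recorded routinely by the research team and submitted for assessment of relatedness as part of the study protocol".
- Recording: "All AEs, related adverse events (RAEs) and SAEs will be recorded using a standard template and reported in line with standard operating procedures".

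The Primary outcomes section includes the safety of both interventions, assessed through review of records and presented descriptively by group.

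**The concern.** Seriousness describes what an event led to. Expectedness describes whether it was foreseen. A definition that requires both lets a foreseen event with a grave outcome be filed as non-serious.

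This matters here for three reasons. Table 1 selects people who have difficulty with walking or balance, and one arm is then encouraged to be more active, so an injurious fall is the obvious serious harm to compare. Safety belongs to the primary outcome domain. The Discussion also says that the data will inform a phase three trial, so an SAE count that is low partly because of its definition could be carried into that trial's safety planning.

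**Working it through.** No calculation reproduces or refutes this point, because it concerns a definition. The check is to apply the wording to the events that the section itself discusses.

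**Step 1: the rule as written.** SAE = untoward AND unexpected AND at least one seriousness criterion. AE = untoward.

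**Step 2: apply it.**

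| Event | Seriousness criterion met? | Called expected in the section? | SAE as written | SAE by seriousness alone |
|---|---|---|---|---|
| Fall without injury | No | Yes | No | No |
| Fall, fracture, admission | Yes (hospitalization) | The fall: yes. The fracture and the admission: foreseen as likely, but not given that label | Unclear; no if expectedness of the fall carries over to its consequence | Yes |
| Respiratory admission | Yes (hospitalization) | Foreseen as likely, but not given that label | Unclear; no if foreseen is taken to mean expected | Yes |
| Unforeseen admission | Yes (hospitalization) | No | Yes | Yes |

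The two definitions disagree, or may disagree, only in the second and third rows. Those are the two kinds of admission that the section names as most likely.

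**Step 3: look for text that settles those rows.** The sentence directly after the definition sets possible hospitalization against the statement that no SAEs are anticipated. That makes sense only if such an admission would be an SAE. But the admissions then named as likeliest are ones the definition can exclude. The section therefore points both ways, and nothing elsewhere in the article resolves it.

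**Step 4: what happens to an event left out of the SAE category.** It stays on record as an AE. If it is a fall, it is also reviewed for relatedness. That review asks whether the research caused the fall; it does not assign seriousness. Falls are an outcome in Table 2, with frequency, circumstance and severity recorded at all three assessments. The between-arm falls analysis in the Exploratory statistical and health economics analysis section models the number of falls, so it does not separate a harmless fall from one causing a fracture.

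**Step 5: scale.** The article gives no rates of falls, fractures or admissions, so no expected number of misclassified events can be derived. As an illustration only: 62 participants allocated 1:1 is 62 / 2 = 31 per arm, and one participant moved into or out of the SAE category changes that arm's proportion by 1 / 31 = 3.2 percentage points. With arms of this size, a single classification decision is visible in the comparison.

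**The case against.** The strongest opposing case is that the wording is loose but little depends on it.

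- *The literal exclusion is only one reading.* This stands. Only falls are called expected; neither fractures nor respiratory admissions are. The sentence on likely admissions is limited to unrelated ones, so a fracture from an intervention-related fall could still be reported as a related SAE. The sentence on anticipated SAEs also suggests that the authors regard admissions as possible SAEs. A reader might infer that serious falls are definitely not counted as SAEs. The documents do not support that; they support saying that such falls can be left out.
- *Nothing is lost.* This also stands. Besides the AE records and the relatedness review, falls are asked about at visits and calls in both arms, kept in diaries and analysed between arms, and service use is recorded. A reader might infer that a between-arm difference in injurious falls would go unseen. It would not: it could be missing from an SAE count, but the severity data needed to show it are collected.
- *No decision uses the SAE count.* Correct for the article. The feasibility thresholds concern retention, and no stopping rule or test shown uses SAEs. This limits the consequence, but the count is still a natural summary of safety in a primary outcome domain.
- *The operating procedures and template may separate the attributes.* Possibly; they are not shown. But the definition has not been left to another document. It is stated here, and a procedure that defined SAEs by seriousness alone would conflict with it.

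One further inference should be resisted. The section lists minor soreness or strain after starting activity as an expected related event, which might suggest that expectedness removes more serious events from the activity arm. That text concerns minor events, so it does not show any such imbalance.

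**Conclusion.** The definition is wrong as written and is at odds with the sentence that follows it. Read literally, it can keep a fall leading to fracture and admission out of the SAE category, and it leaves eight sites to decide whether a foreseen consequence of an expected event is itself expected. Identical events may be classified differently, and SAE counts by arm may be understated.

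The fault lies in classification and counting, not in capture. Its size cannot be determined from the article. The direction is clearer: adding a condition to a definition can only remove events from it, so any error lowers the count. The conclusion assumes that sites apply the published definition; if the unseen forms already record seriousness separately, the practical effect is smaller, but the text still needs correcting.

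**What to change.** 1. Delete *and unexpected* from the SAE definition, leaving the seriousness criteria exactly as listed.
2. Record expectedness and relatedness for each event as separate attributes, each assessed independently of seriousness.
3. Reconcile the sentence on anticipated SAEs and hospitalization with the definition, so that sites can tell that an admission meeting a listed criterion is an SAE whether or not it was foreseen.
4. Tabulate all SAEs and all injurious falls by arm, showing expectedness and relatedness alongside. The fall-severity data already planned supply the second table.

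The cost is two words in the definition, matching changes to the template and operating procedures, a note to sites, and a few more SAE forms. Events already recorded should be reclassified under the revised definition, which the existing AE and falls records should allow. No outcome, sample size or clinical procedure changes.

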### Exploratory statistical and health economics analysis

Summary statistics of demographics (age, gender, height and weight) and disease burden scores will be reported. Descriptive data will include an evaluation of eligibility, recruitment, retention rates and acceptability of, and adherence to the intervention, with 95% confidence intervals. Descriptive analysis of adherence rates according to baseline measures will be analyzed to inform the assessment of mediators of the intervention. The completion of outcome measures and assessments will also be reported. Graphical illustration will be used to check distributions of outcome data.

Successful adherence to the intervention will be defined as having completed visit one, two and three with their activity coach. Further aspects of adherence will be measured by the percentage of exercise and falls diaries completed by participants, and the percentage of participants who use the physical activity workbooks and exercise DVD. Descriptive analysis of goals set will be considered in relation to adherence. If retention rates are greater than the estimated 75%, we will consider this intervention to be feasible. If the proportion retained is less than this but greater than 65%, we will consider adjusting the intervention to increase this in future investigations. A retention rate lower than this would require substantial changes to the intervention and therefore would require further piloting.

As it is our intention to inform future confirmatory trials, we will explore the feasibility of outcomes as applied in this trial and this population. We will consider internal reliability of all summated scales and assess both construct and convergent validity of scales not previously used in HD. In particular, the ordinal scoring criteria for the PPT were developed for application in frail elderly people. The distribution of the timing measures will be specifically explored in order to either validate existing categories or define new categories specific for application in an HD population. Other measures that will be investigated for their application in HD include the IPAQ short form, SEIQol-DW, Life space assessment, ICECAP-A and the Lorig self-efficacy scale. Finally, we will compare the self-reported falls reported by patients at assessments (recall), and the falls reported by patients in their weekly health and falls diaries, in an attempt to validate falls reporting in this population.

A public sector, multi-agency perspective will be used for the economic evaluation. Exploratory health economics analyses will be conducted to investigate the patterns of participants’ health and social care service use, and the associated costs. Information on health and social care service use will be collected using a Client Service Receipt Inventory
[23]. The cost of developing the intervention, training staff and the delivery of the intervention will be calculated. A cost-utility analysis using the EQ-5D-5 L
[24] will be conducted to assess the incremental cost-effectiveness of the physical activity intervention compared to the social contact intervention, along with a cost-effectiveness analysis using the ICECAP-A
[25]. We will further present a cost-consequence analysis of costs and a range of outcome measures for the participants. We will conduct two sensitivity analyses related to staff costs: firstly, we will test the effect of using staff at a higher and lower grade to conduct the training to deliver the intervention; secondly, we will test the effect of using staff at a higher and lower grade to deliver the intervention. We will also conduct a sensitivity analysis removing the cost of supplying a DVD player to participants.

### Process evaluation

At the end of the study, participants will be asked to complete an end of study questionnaire that focusses on their views of the trial and of the intervention. We will also attempt to contact any participants who drop out of the intervention to ascertain reasons for discontinuing. Coaching staff will be interviewed to gather their opinions on delivery of the intervention. Topics will include challenges to intervention delivery, perceived successes, barriers to implementation and suggestions on how to improve the intervention process. All the interviews will be digitally audio recorded and transcribed verbatim for further analyses. We will employ standard thematic analysis techniques, which is essentially a process of summarization, categorization and counting frequency of responses. The transcripts of interviews will be closely examined to identify themes and categories. Codes will be applied to these broad themes, which will then be broken down further into sub-codes. Agreement on concepts and coding will be sought between members of the research team to ensure reliability. We will identify commonly expressed themes as well as unusual cases. A proportion of the data (20%) will be coded by two different team members to check on reliability of the coding scheme. Interviewing will be iterative; where new themes emerge we will incorporate them into subsequent interviews.

### Dissemination policy

Results of this trial will be reported in the first instance to the funders, and then communicated to participants and relevant health professionals in a series of open access publications within nine months of the end of the data collection. Authorship will follow the trial publication policy that has been developed based on British Medical Journal rules on authorship and contributorship.

## Discussion

While regular and sustained physical activity has the potential to benefit patients with neurodegenerative conditions such as HD, there are a number of disease-specific factors, which make it particularly challenging to establish regular exercise in this population. The intervention described in the current trial was developed following wide-ranging consultation with people with HD and their families, so as to give due consideration and to accommodate the known limiting factors in this population. The interpersonal interactions of the intervention are underpinned by the concepts of SDT placed within a broader BCW framework. The associated logic model aids in providing a consistent structure for intervention delivery and facilitates testing of short and potentially longer term outcomes in relation to the individual elements of the intervention. A major emphasis of the intervention is the development of highly individualized exercise plans. The exercise plans are therefore determined by individual needs and goals that may change with disease progression. Such an approach is important in a neurodegenerative disease so as to promote longer term disease management in a continually changing arena.

Any physical activity or exercise-based intervention relies heavily on the interaction between the provider (coach, therapist and/or trainer) and the participant. As a result, any improvement that may be seen may be, at least in part, attributed to social interactions. It is therefore important for intervention trials to incorporate active compactor arms to help reveal the specific effects of each intervention. Here, rather than having a traditional, usual care control group, the trial has a comparator arm which involves half of the participants receiving a series of social interaction sessions which are time-matched with the coaching sessions delivered in the intervention group.

We will consider the acceptability of the interventions to participants; the ability of centers to recruit participants; the willingness of participants to be randomized; the number of eligible participants; the acceptability of the measures and the time taken to collect data. In this trial, we have developed an innovative approach to data collection, monitoring and site support using iPads. In addition to using iPads as a data entry tool, site staff are able to use the device to hold regular video conference calls with research staff, enabling a greater level of day-to-day support and guidance. The iPads are also being used to make audio recordings of intervention sessions, in order to monitor fidelity. We have implemented a variety of measures to minimize loss to follow-up and missing data
[36]. From a design perspective, we have explicitly considered the burden with respect to timings of assessments and intervention sessions. The intervention is delivered in the home, which may be another factor to minimize loss to follow-up. Adverse events are systematically documented and, if participants choose to discontinue the intervention, sites are encouraged to continue with outcome assessments wherever possible. Finally, data monitoring is extensive to ensure minimization of missing forms or data, and analysis will consider imputation methods as required.

Although measures of effectiveness and cost are being collected, this trial is not powered for full effectiveness analysis. The data gathered here will inform the design (including sample size calculations) and delivery of a confirmatory phase three trial. In order to ensure repeatability in confirmatory trials, reporting will follow the template for intervention description and replication (TIDieR) reporting guidelines for description of interventions
[37], and the Consolidated Standards of Reporting Trials (CONSORT) extension for non-pharmacological interventions
[38].

## Trial status

The trial opened to recruitment in May 2014, with recruitment expected to end in July 2015.

## Abbreviations

AE: Adverse event
ANCOVA: Analysis of covariance
BCW: Behavior Change Wheel
CACE: Complier-average Causal Effect
CONSORT: Consolidated Standards of Reporting Trials
CSRI: Client Receipt Inventory Service
EHDN: European Huntington’s Disease Network
HD: Huntington’s disease
ICECAP-A: ICEpop CAPability measure for Adults
IPAQ: International Physical Activity Questionnaire
ITT: Intention to Treat
NHS: National Health Service
NIHR CRN: National Institute for Health Research Clinical Research Network Portfolio
PAS: Perceived Autonomy Support
PI: Principal Investigator
PPT: Physical performance test
RAE: Related adverse event
SAE: Serious adverse event
SEIQoL-DW: Schedule for the Evaluation of Individual Quality of Life
UHDRS: Unified Huntington’s Disease Rating Scale.
